## Background

Walking is an important human activity which enables us to be productive and participative members of a community. Normal walking speed for older persons is 1.3 m/s [1] and walking capacity measured by the distance covered in 6 minutes is 576 m for men and 494 m for women [2]. After stroke, although the majority of patients leave rehabilitation with some level of independent walking, many have residual walking disabilities. Walking speed of community-dwelling people after stroke has been reported to be around 0.5 m/s with studies reporting a range between 0.3 and 0.8 m/s [3-7]. Walking capacity has also been found to be markedly reduced with 6-minute distance being reported as around 250 m ranging between 40 and 400 m [8,9]. This reduction in walking speed and capacity results in major limitations in community participation. For example, Hill and colleagues [3] found that many individuals after stroke could not walk fast enough to cross the road safely or far enough to do the shopping. The consequence of poor walking ability is widespread, affecting the person and their family and friends. Poor walking ability has been found to reduce quality of life with a reduction in participation in activities outside the home and therefore social isolation. In particular, patients fear dependency more than anything else after a stroke and the ability to walk independently has been found to provide the greatest protection against dependency [10]. A community ambulator is less dependent on family and friends not only for assistance with household tasks but also for assistance with community participation.

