**Figure 1 F1:**
[figure not shown]
**Improvements of 80 m in 6-min distance following a one-month treadmill and overground walking program (solid = experimental, dotted = control) with subsequent relapse over three months (from Ada et al **[17] with permission).

In summary, the main objectives of the AMBULATE trial are to determine (i) whether a 4-month treadmill and overground walking program is more effective than a 2-month program, compared to control, in improving walking capacity, health and community participation and (ii) the "threshold" walking speed that results in sufficient walking capacity that makes walking self-sustaining.

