### Sample size

210 participants will be recruited. The sample size has been calculated to reliably detect a treatment effect size of a 50 m difference in walking capacity with 80% power at a two-tailed significance level of 0.05 on any pairwise comparison. This effect size has been derived from the walking capacity of a population of community-dwelling stroke patients who took part in the previous treadmill walking program [17]. On entry to this randomised controlled trial, the distance walked in 6 minutes was 280 (SD, 100) m using the same measurement procedure to the present proposal. The smallest number of participants to detect a 50 m difference between two groups estimated from independent samples is 63 participants per group, i.e., 189 participants in total. On the assumption that about 10% of the participants may drop out during the course of the study, we have set a target of 210 participants in total.

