### Statistical analysis

The variables that reflect walking capacity, community participation and quality of life will be analysed by pairwise comparisons between the three groups using the Students' t-test, or Wilcoxon's rank-sum test if it is clearly not normally distributed.

The other health variables: number of falls, number of readmissions to hospital, comorbidities, and number of visits to the doctors will be expressed as a proportion of events per person and analysed by pairwise comparisons between the three groups using the Chi square test.

To ascertain the threshold of post-intervention walking speed that results in the maintenance of 80% of predicted 6-min distance at 12 months, receiver operating characteristic (ROC) curves will be constructed. Youden's Index will be used to determine the cut-off point for walking speed at the end of the programs that gives the best combination of specificity and sensitivity.

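### The Youden cut-off for objective (ii) is the speed at which the chance of success equals the trial's overall success rate, so it need not be a speed at which self-sustaining walking is likely

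*Protocol article*

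**What the plan says.** The objectives, given in the Abstract and at the end of Background, include finding the threshold "walking speed that results in sufficient walking capacity that makes walking self-sustaining". In the last paragraph of Statistical analysis, success is defined by "maintenance of 80% of predicted 6-min distance at 12 months, receiver operating characteristic (ROC) curves will be constructed", and the threshold is then fixed by a rule: "Youden's Index will be used to determine the cut-off point for walking speed at the end of the programs". The article presents this cut-off as the best trade-off between sensitivity and specificity.

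It states no expected success rate, no probability of success that the threshold should deliver, and no definition of predicted distance. The only reference distances it gives are in Background: "576 m for men and 494 m for women". Sample size reports that, at entry to the previous trial, "the distance walked in 6 minutes was 280 (SD, 100) m".

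**The concern.** Objective and rule ask different things. The objective wants a speed at which a person can expect to have enough capacity at 12 months. Youden's index weighs sensitivity and specificity equally and takes no account of how common success is. The speed it selects separates successes from failures well, but the chance of success at that speed is only the average chance in the sample. If success is uncommon, a participant who reaches the reported threshold may still be unlikely to meet the trial's own criterion. The chance attached to the threshold also depends on the success rate among those enrolled.

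At stake is what one of the two main objectives can conclude. A Youden speed reported as the one that makes walking self-sustaining would claim more than the method shows. Splitting the distance also discards how far each person is from the criterion.

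**Working it through.** **The plan's own figure.** The only calculated figure is the sample size, and it reproduces. n per group = 2 × (1.960 + 0.842)² × (100/50)² = 62.8, rounded up to 63; 3 × 63 = 189; 189/0.90 = 210. No figure is given for the ROC objective. The two training groups would supply 2 × 63 = 126 completers.

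**Where Youden's index puts the cut.** Let f1 and f0 be the densities of end-of-program speed among successes and failures, and π the overall success rate.

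- J(c) = Se(c) + Sp(c) − 1, where Se(c) is the area of f1 above c and Sp(c) the area of f0 below c.
- dJ/dc = −f1(c) + f0(c) = 0, so f1(c) = f0(c) at the maximum.
- By Bayes' rule, P(success | speed = c) = π f1(c) / [π f1(c) + (1 − π) f0(c)] = π.

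This is a population result for densities that cross once. More data or a smoothed ROC curve does not remove it.

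**Inputs for its size.**

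- From Background: norms of 576 m and 494 m. 80% of these is 460.8 m and 395.2 m. Treating them as the predicted values is an assumption.
- From Sample size: mean 280 m and SD 100 m at entry, and a 50 m design difference.
- From the Figure 1 caption: an 80 m gain in the previous trial. Background says that it was not maintained 3 months later.
- Assumed: 12-month means of 280, 330 (280 + 50) and 360 m (280 + 80); SD still 100 m; normal distributions; half men; speed-distance correlation 0.5 to 0.85.

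**Success rate.** π = 0.5 × P(N(mean, 100) > 460.8) + 0.5 × P(N(mean, 100) > 395.2).

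- Mean 280 m: 0.5 × 0.035 + 0.5 × 0.125 = 8.0%
- Mean 330 m: 0.5 × 0.095 + 0.5 × 0.257 = 17.6%
- Mean 360 m: 0.5 × 0.157 + 0.5 × 0.362 = 26.0%

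At a mean of 330 m, a 30% or 70% share of men gives 21% or 14%.

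**Direct check.** Maximising J over a fine grid of speeds, without using the identity, gave:

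| 12-month mean | Chance at the cut (r = 0.5, 0.7, 0.85) | Chance at or above the cut (r = 0.5, 0.7, 0.85) |
|---|---|---|
| 280 m | 8.0% at each | 16%, 22%, 30% |
| 330 m | 17.6% at each | 30%, 38%, 47% |
| 360 m | 26.0% at each | 41%, 49%, 58% |

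In simulated samples of 126 (mean 345 m, correlation 0.75), the true chance of success at the estimated cut-off had a median of 23%, with a 95% range of 10% to 42%.

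**Sensitivity to the predicted value.** With these norms, a 50% success rate needs a 12-month mean near (460.8 + 395.2)/2 = 428 m, which is 148 m above 280 m. If predicted values were 20% lower, a mean of 360 m would give a success rate, and so a chance at the cut, of 57%.

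**The case against.** The strongest defence is that the plan names its target, the best balance of sensitivity and specificity, and Youden's index delivers exactly that. A sufficiency criterion calls for some division into success and failure, and ROC analysis is a recognised way to find a cut-off. This stands as far as it goes: the 80% criterion is legitimate, and the Youden cut is a fair description of discrimination. It does not make that cut the speed that brings about sufficient capacity, which is how the objective and the analysis paragraph describe it.

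Three stronger readings are tempting, and the article supports none of them.

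- *Most people who reach the threshold will fail.* The identity alone does not give this. It needs a success rate below 50%, which the article never states. The Background norms are not said to be the predicted values, and lower individual predictions could take the rate above 50%. The low chance also belongs to people walking at the cut. Among those at or above it, 58% succeed at a mean of 360 m and correlation 0.85, even with the Background norms.
- *The Youden speed is too low.* This presumes a required probability, such as 50%, that the article does not set. With a success rate of 57%, the Youden speed lies above the 50% speed.
- *Youden should be replaced by the speed at which expected distance reaches 80% of predicted.* In the assumed model that speed is itself about a 50% point, and only about 0 to 27 of 126 trained completers would exceed it.

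**Conclusion.** The concern holds as a mismatch between objective (ii) and its analysis rule. At population level with a single crossing point, the chance of success at the Youden cut-off equals the overall success rate, whatever that rate is, so the cut-off need not be a speed at which success is likely.

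Its size is conditional. With the Background norms as predicted distance, a 12-month mean of 280 to 360 m, SD 100 m, normality and equal numbers of each sex, the chance is about 8% to 26% at the cut-off. It is about 16% to 58% at or above it for correlations of 0.5 to 0.85. Lower predicted values would raise both.

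The change should be made, because it alters what a main objective can conclude. The primary comparison of 6-minute distance is unaffected.

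**What to change.** Add to the last paragraph of Statistical analysis:

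- 12-month distance, as a percentage of predicted, will be modelled on continuous walking speed at the end of the program.
- The estimated probability of reaching 80% of predicted will be reported across the observed speeds with 95% confidence intervals.
- The speed at which a prespecified probability is reached will be reported with its interval, if it lies within the observed range.

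Keep the ROC curve and Youden cut-off as a description of discrimination. Report the probability of success at and above the cut-off, and do not describe it as the speed that makes walking self-sustaining.

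This needs no new data or participants, only a little more analysis and an assumption about the shape of the relation that the same data can check. Few participants may lie near a high-probability speed, so the interval there may be wide.

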## Discussion

This research has the potential to make a large difference to the quality of life of many stroke survivors. By improving stroke survivors' walking ability, it is likely also to improve their general wellbeing by promoting better health and greater community participation. Furthermore, if stroke survivors can reach a point where their walking and community participation is self-sustaining, this will reduce the burden of care on family and friends as well as the economic burden on the health system. Given the major demographic shift in developed nations involving significant growth in the aged population, this research will make an important evidence-based contribution to the promotion of healthy ageing.
